## Materials and methods

2

### Design

2.1

This research is a pilot single-blind RCT. The participants are families of children who have been diagnosed with asthma at a specialized hospital located in the Inner Mongolia Autonomous Region of China. The study procedure and the method of grouping are presented in **Figure 1**.

**Figure 1 f1:**
[figure not shown]
Flow chart of patient recruitment and study implementation.

### Randomization and blinding

2.2

In this study, the randomization procedure uses a computer-generated sequence of random numbers. Patients will be assigned to the intervention and standard care groups in a 1:1 ratio. This randomization process will take place prior to patient admission. The aim is to ensure that each patient is assigned to the appropriate study group in a predefined order, thus ensuring randomization and fairness of allocation. When patients are admitted to the hospital, they will be assigned a unique code. This code is consistent with the sequence of random numbers and ensures smooth and consecutive enrollment of patients. Once randomization is complete, patients are directed to the appropriate hospital room based on their grouping. Specifically, patients in the intervention group are sent to Ward A, while those in the control group are sent to Ward B to prevent any possible cross-talk between the different interventions.

To ensure the confidentiality of the allocation sequence, an independent team member will be responsible for the randomization process and be neither involved in participant registration nor in intervening in the allocation. This is to prevent disclosure of the sequence during the course of the study. This team member then forward the allocation results to the intervention team. By doing this, both the participant enrollment team and the intervention team know nothing about the allocation in advance.

Finally, given the uniqueness of the AI-HEALS intervention in this trial, complete blinding of participants and therapists will be infeasible. This limitation may introduce biases such as performance bias due to participants’ awareness of their treatment allocation and detection bias from therapists’ knowledge of the implemented intervention. To minimize these biases, a series of measures will be implemented to reduce bias impact on this study. First, the identities of all intervention and control group participants will remain concealed until study completion. Second, an independent team member not involved in participant enrollment or intervention delivery will oversee the randomization process. This individual will directly forward allocation results to the intervention team to ensure both the enrollment and intervention teams remain unaware of group assignments in advance. Third, intervention group patients will be hospitalized in Ward A while controls occupy Ward B to prevent cross-contamination between groups. Finally, to further mitigate bias, research assistants blinded to group assignments will collect study data. Additionally, data analysts will remain blinded to group allocations during the analysis phase. Data will be coded and kept confidential throughout the study to preserve the integrity of the blinding process.

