### Recruitment

2.5

This study endeavors to recruit families of children with asthma who satisfy the inclusion and exclusion criteria at the target hospital. The recruitment process will be spearheaded by the hospital’s medical team. They will identify and extend invitations to eligible patients when they are admitted to the hospital. Subsequently, the research team will carry out an initial face-to-face communication with the patients. During this communication, detailed information about the study’s objectives, procedures, potential benefits, and possible risks will be provided. Eligible patients will be invited to the hospital for a thorough health assessment. This assessment includes a detailed review of the child’s asthma history and symptoms. After making certain that the patients have a full understanding of the study and answering any questions they might have, the families of children with asthma will be requested to sign an informed consent form. Only those who sign the informed consent form will be formally enrolled in the study.

Participants will receive a three-month AI-HEALS intervention. Additionally, this study employs fixed measurement agents to ensure reliability of self-report measures. Specifically, the same family member who initially accompanied the child to the first hospital visit will be designated to complete all self-report assessments throughout the study period to maintain measurement consistency. To encourage maximum participation, as an incentive for their involvement, all participants will receive a free medical consultation after the study.

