#### Secondary outcomes

2.9.2

Physiological Control of Children: The assessment indicators cover multiple aspects. In terms of pulmonary function, key parameters such as pulmonary ventilation function and expiratory flow rate will be detected by professional equipment; the average number of days with asthma symptoms, record the number of days when children experience asthma-related symptoms within a certain period; the number of nights awakened due to asthma symptoms; the number of days with activity limitations due to asthma; the number of days per week requiring inhaled bronchodilators for symptom relief; height, weight, waist circumference, body mass index (BMI); the 30 - day readmission rate; the length of hospital stay.Parental Behavior Changes: Parental behavioral changes will be measured using specific instruments, including a self-developed questionnaire to assess frequency and exposure to smoking and alcohol consumption; the Pittsburgh Sleep Quality Index Short Form (PSQI-SF) to evaluate sleep patterns; and the EQ-5D-5L (EuroQol-5 Dimensions 5 Levels) scale for measuring overall quality of life.Parental Social Cognition and Psychology: Self-efficacy; depression, anxiety, stress levels; social support.

In addition, the recruitment rate, dropout rate, and reasons for withdrawal will be collected. During the data analysis phase, in order to assess the homogeneity of the data, the demographic characteristics and study outcomes of those who dropped out will be compared to determine whether the dropout situation has an impact on the overall effectiveness of the study.

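### One ward per arm makes any ward effect inseparable from AI-HEALS, leaves in-hospital blinding unsecured, and does not exclude that the arm is visible before consent

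*Protocol article*

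**What the plan says.** **Ward and arm.** Section 2.2 (Randomization and blinding) assigns wards by group: "patients in the intervention group are sent to Ward A, while those in the control group are sent to Ward B". The same section repeats the rule as one of its measures against bias: "intervention group patients will be hospitalized in Ward A while controls occupy Ward B to prevent cross-contamination between groups".

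**Timing of allocation.** Section 2.2 says: "This randomization process will take place prior to patient admission". It continues: "When patients are admitted to the hospital, they will be assigned a unique code", a code that matches the random sequence, and then "Once randomization is complete, patients are directed to the appropriate hospital room based on their grouping".

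**Timing of consent.** Section 2.5 (Recruitment) has the hospital's medical team invite eligible families when the child is admitted. A face-to-face talk, a health assessment and the consent form follow, and "Only those who sign the informed consent form will be formally enrolled in the study". Table 1 lists eligibility screen, consent and allocation in that order, all at time 0.

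**Blinding.** Section 2.2 accepts that participants and therapists cannot be fully blinded. It says that group identities stay concealed until the study ends and that "research assistants blinded to group assignments will collect study data". It also says that an independent team member runs the randomization and that the enrolment team has no advance knowledge of it.

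**Outcomes and model.** C-ACT and lung function are measured at baseline, discharge and 3 months (Table 1). Secondary outcomes include 30-day readmission and "the length of hospital stay" (section 2.9.2). The models in section 2.12 have family-level random intercepts and no ward term.

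**The concern.** The ward rule is meant to prevent contamination, but it puts three things at risk.

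1. **Attribution.** Standard care in section 2.7.1 includes structured education on condition management, adherence and lifestyle, the same behaviours that AI-HEALS aims to change. If the two wards differ in how this is delivered, the difference is counted as an effect of AI-HEALS.
2. **Blinding.** Families and therapists are unblinded, so the single-blind label rests on data collectors and analysts. A collector who sees a child on the ward, and knows the rule, knows the arm.
3. **Selection.** If a child is placed by group before the family has consented, the placement can tell the family and the recruiting staff which arm it is. Who then enrols may depend on the arm, and randomization no longer protects the comparison.

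The pilot's estimates are likely to inform any later trial, and a ward effect would be carried along unseen.

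**Working it through.** **1. Can ward and arm be separated?** Let A = 1 for AI-HEALS and W = 1 for Ward A. Under section 2.2, W = A for every child. A model with both terms has two identical columns, so only the sum of the ward and treatment effects can be estimated. The family random intercept in section 2.12 does not change this, and adding a ward term would not help. The conclusion needs no numerical assumption.

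**2. Which outcomes are exposed?**
- Length of stay and lung function at discharge: directly, because both are determined or measured at the end of the stay on the arm-specific ward.
- C-ACT at discharge: less directly. Its parent items look back four weeks (section 2.11) and may largely cover time before admission unless stays are long.
- 30-day readmission and 3-month C-ACT: only as far as ward effects, such as lasting teaching, persist after discharge.
- Parenting style, social support and self-efficacy: there is no evident reason to call these products of the ward.

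**3. How large could it be?** The plan gives no figure to reproduce, so this is an illustration.

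Inputs from the plan: n = 25 evaluable per arm (section 2.4); two-sided alpha 0.05 (section 2.12). Assumed: a ward intraclass correlation ρ of 0.01, 0.02 or 0.05, and a normal approximation.

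- True variance of the difference: 2σ²[(1−ρ)/n + ρ]
- Variance that an analysis without ward estimates: 2σ²(1−ρ)/n
- Variance ratio: 1 + nρ/(1−ρ); SE ratio R is its square root
- Actual type I error: 2[1 − Φ(1.96/R)]

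For ρ = 0.02: 1 + 25 × 0.02/0.98 = 1.51; R = 1.23; 1.96/1.23 = 1.59; type I error 0.11.

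| Assumed ρ | Variance ratio | SE ratio | Actual type I error |
|---|---|---|---|
| 0.01 | 1.25 | 1.12 | 0.08 |
| 0.02 | 1.51 | 1.23 | 0.11 |
| 0.05 | 2.32 | 1.52 | 0.20 |

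The same point can be made with a fixed ward difference and no treatment effect. With SE = √(2/25) = 0.283 SD, an assumed ward shift of 0.2, 0.3 or 0.5 SD gives a false-positive rate of 0.11, 0.19 or 0.42.

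**4. Is the order of steps consistent?**

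| Source | Order stated |
|---|---|
| Section 2.2 | Randomization before admission; code at admission; room by group |
| Section 2.5 | Admission and invitation; information; health assessment; consent; enrolment |
| Table 1 | Screening; consent; allocation |

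If section 2.2 is taken at its word, the arm is fixed before the family is approached, which does not fit Table 1. If randomization before admission means only that the sequence is generated then, all three can agree, but the text does not say so. Concealing the sequence does not settle it, because placing the child in Ward A or B would itself disclose the arm.

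**The case against.** **Allocation is said to be concealed.** Section 2.2 gives the sequence to an independent member and denies the enrolment team advance knowledge. Figure 1 is not available in the text reviewed and may show the order of steps. This stands as evidence of intent. A reader might infer that families do consent knowing their arm; the documents do not support that. They support only an unresolved inconsistency that leaves it possible. Likewise, section 2.3.1 excludes children who fail diagnostic confirmation but gives no timing, so exclusion with the arm known cannot be asserted.

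**Data collectors may not know the ward rule.** A reader might infer that the blinded assessors all see the arm. The plan does not say where data are collected or who knows the mapping, and nothing shows that 3-month assessors would know the earlier ward. What stands is that the arm can be inferred in hospital. C-ACT is answered by the child and the parent, who are unblinded anyway, so assessor blinding adds less for the primary outcome.

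**The wards may not differ.** Both are in one hospital, and the plan does not say whether staff are shared. No ward difference is documented, so the size is unknown. The lack of identifiability remains.

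**It is a pilot.** Section 2.4 says the trial is not designed for hypothesis testing. But the abstract and the Discussion make improved asthma control the main aim, and section 2.12 sets two-sided tests at 0.05. The objection lessens the weight of the type I error figures but does not remove bias from the estimates.

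**Conclusion.** The point holds in three parts of differing strength.

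- **Confounding: certain.** Arm and ward coincide by design, and no analysis can separate them. It would go too far to call every discharge measure a product of the ward, or to treat the 3-month C-ACT as compromised whether or not ward effects last.
- **In-hospital blinding: not secured.** This is an inference from the ward rule, limited to assessments during the stay.
- **Order of allocation and consent: contradictory as written.** Disclosure before consent is possible but not shown.

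The type I error of about 8%, 11% or 20% (SE ratio 1.12, 1.23 or 1.52) rests on assumed ward correlations of 0.01, 0.02 and 0.05 with 25 per arm. The documents give no such correlation. The matter should be settled before enrolment, because the confounding cannot be undone afterwards.

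**What to change.** 1. Reconcile sections 2.2 and 2.5 with Table 1. State that the sequence is generated in advance, if that is what is meant, and that each child's allocation is released only after signed consent, confirmed eligibility and baseline C-ACT.
2. Delete the Ward A / Ward B rule, so that bed assignment does not depend on arm.
3. Limit contamination by opening AI-HEALS only to the WeChat account of the caregiver allocated to it.
4. If the wards stay separate, state that ward and intervention effects cannot be separated. Report length of stay and discharge measures descriptively, not as between-arm effects, and withdraw the claim of blinded data collection in hospital.

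The cost is a reordering of steps, a revision of the text and an access list for the account. The small downside is that families sharing a ward may see or discuss the app; account control limits this but does not abolish it.

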### Study sample

2.3

This research will adopt a continuous enrollment method to recruit families of children diagnosed with asthma from April 2025 to December 2026. The detailed inclusion and exclusion criteria are as follows:

#### Inclusion criteria

2.3.1

Age range: The children should be between 6 and 13 years old.Diagnostic criteria: Children enrolled in this study must be diagnosed with asthma by a specialized pediatric pulmonologist and currently receiving standardized treatment. The diagnostic criteria are based on two components: 1) clinical manifestations including recurrent wheezing, cough, and shortness of breath (particularly exacerbated at night or post-exercise) (26); and 2) objective pulmonary function test results demonstrating reversible airflow limitation. Specifically, for children with recurrent cough and/or wheezing: forced expiratory volume in one second (FEV_1_) must be <80% of predicted value with an FEV_1_/forced vital capacity (FVC) ratio <0.8, and following inhalation of a short-acting β_2_-agonist, FEV_1_ increases by ≥12% and absolute improvement ≥200 mL (26). Children not meeting both diagnostic components will be excluded after physician confirmation.Parental involvement: The child’s primary caregiver must be willing and capable of participating in all study-related activities, including uploading daily life records (e.g., medication adherence logs, physical activity records), engaging in interactive health consultations with AI-HEALS, receiving and reviewing health education articles delivered by the system, and completing all study assessments.Technology requirements: The parents must possess a smartphone that can access WeChat and be willing to utilize the platform to receive and reply to the intervention content of the study.

#### Exclusion criteria

2.3.2

Severe comorbidities: Children diagnosed with specific severe cardiovascular diseases (e.g., congestive heart failure, uncontrolled arrhythmia, or myocardial infarction) or severe pulmonary diseases (e.g., cystic fibrosis) within the past six months will be excluded from this study. These conditions can significantly impair respiratory function and potentially influence intervention outcomes.Other chronic diseases: Children with other long-term chronic conditions that demand continuous treatment and could interfere with asthma management, like cystic, will also be ineligible.Participation in other asthma studies: Children who are currently taking part in other asthma intervention studies will not be included.Psychological or behavioral issues: Children with severe psychological or behavioral issues, such as schizophrenia, severe autism spectrum disorder, or other mental illnesses requiring acute hospitalization, will be excluded. These conditions can impede patients’ continuous participation in intervention activities and compromise the integrity of data collection.Language barriers: Families that are unable to understand or communicate in basic Chinese will not be part of the study.

#### Withdrawal criteria

2.3.3

Voluntary withdrawal: Families have the option to withdraw from the study for personal reasons. For example, they might face scheduling conflicts that prevent them from devoting the necessary time to the study, or their interest in participating may wane over time.Severe adverse events: Participants who encounter serious adverse events, such as severe physical illnesses or acute incidents like a heart attack or severe infection, which necessitate the interruption of the intervention, will be removed from the study.Changes in treatment: If a participant’s condition changes, or they receive medical advice to alter their treatment plan in a way that conflicts with the study intervention, they will be excluded.

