### Informed consent

2.6

The informed consent procedure will be conducted in an open, transparent manner and will strictly adhere to ethical standards. Parents or guardians of children meeting the inclusion and exclusion criteria will receive a comprehensive written explanation describing the research objectives, procedures, potential risks and benefits, as well as data privacy protection measures. This includes detailed information on how their data will be collected, stored, and protected. We will ensure that all data is securely stored in encrypted form on protected servers, accessible only to authorized research team members during the study period, and properly destroyed after the study concludes. Participants will be given sufficient time to carefully read the consent form, ask any questions, and provide consent voluntarily. They will be explicitly informed that they have the right to withdraw from the study at any time without any negative consequences. The research team will provide ongoing contact information for consultation, allowing participants to obtain further information or clarification when needed. Throughout the study, we will provide participants with any new information that might affect their decision to continue participation, ensuring continuous informed consent.

Additionally, participants will not face any penalties for deciding to withdraw from the intervention arm. If the intervention has already commenced, patients cannot switch to the control group after withdrawal and will be marked as an attrition case. Where feasible, semi-structured interviews will be conducted with attrited participants to explore reasons for discontinuation. During the informed consent process, participants will be explicitly informed of all available options following withdrawal, ensuring they remain fully aware of their rights and choices throughout the study period.

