#### Primary outcomes

2.9.1

The primary outcome was changes in asthma symptom control, measured using the Childhood Asthma Control Test (C-ACT) at baseline, discharge, and post-intervention. Given the nested longitudinal structure of repeated measurements within families, we employed multilevel negative binomial models to analyze asthma symptom frequency (count data), estimating incidence rate ratios (IRRs) and 95% confidence intervals (CIs).

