
### Statistical analysis

2.12

This study will collect quantitative data through questionnaires and process the data using Microsoft Excel. Data analysis will follow the intention-to-treat principle. For continuous variables, descriptive statistics will show means ± standard deviations or medians and interquartile ranges (P25, P75), depending on the data. Normally distributed continuous variables will be compared using the Student’s t-test or one-way analysis of variance (ANOVA). Non-normally distributed data will be analyzed with non-parametric tests. The normality of the data will be checked using the Kolmogorov-Smirnov test. Categorical variables will be shown as sample percentages (n) and analyzed using the Chi-square test. For missing data, multiple imputation using chained equations (MICE) will be used, with 50 iterations to ensure convergence. The imputation method will be predictive mean matching (PMM), with 5 neighbors and 20 imputed datasets.

In the cross-sectional data analysis, this study will use linear regression, logistic regression, and structural equation modeling (SEM) to examine the relationships between behavioral patterns and mobile health applications. Given the nested structure of parent-child dyads within families, we employed multilevel models with family-level random intercepts to account for within-family correlations. For child health outcomes (asthma-related events and symptoms), a two-level negative binomial model was utilized to estimate IRRs and 95% CIs, adjusting for family-level variables (parents’ parenting styles, household income, marital status) and child-level variables (age, sex). For parental outcomes (continuous data), a two-level linear mixed model was applied to evaluate intervention effects, adjusting for family-level variables (marital status, household income) and parent-level variables (age, education, parents’ parenting styles). *Post hoc* comparisons of estimated marginal means were conducted using the emmeans package to test between-group differences. Model fit was validated through convergence checks, residual analysis, and overdispersion testing for count data. All analyses were performed in R (version 4.3.1; R Foundation for Statistical Computing, Vienna, Austria) using the lme4 package (version 1.1-33). An independent statistician with no conflicts of interest conducted the analysis. All statistical tests were two-tailed, with a significance level of 0.05.

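### The withdrawal rules end participation for children who stop or conflict with the intervention and provide no further outcome collection, so intention-to-treat would rest on imputing 3-month C-ACT values that could have been measured

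*Protocol article*

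**What the plan says.** Three rules act after enrolment.

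- **Serious events (protocol article, 2.3.3).** Participants with serious events "which necessitate the interruption of the intervention, will be removed from the study".
- **Changed condition or treatment (2.3.3).** The rule names a change in the child's condition as a trigger and then covers those who receive "medical advice to alter their treatment plan in a way that conflicts with the study intervention, they will be excluded".
- **Leaving the AI-HEALS arm (2.6).** Once the intervention has begun, "patients cannot switch to the control group after withdrawal and will be marked as an attrition case". Where feasible, these families are interviewed about their reasons. No outcome assessment is mentioned.

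The analysis section (2.12) states: "Data analysis will follow the intention-to-treat principle". For gaps it states: "For missing data, multiple imputation using chained equations (MICE) will be used, with 50 iterations to ensure convergence", by predictive mean matching with 5 neighbours and 20 imputed datasets. The primary outcome (2.9.1) is change in asthma control, "measured using the Childhood Asthma Control Test (C-ACT) at baseline, discharge, and post-intervention". Table 1 schedules C-ACT and lung function for all participants at 3 months.

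The article does address dropout in part. Section 2.9.2 collects the dropout rate and reasons for withdrawal and compares those who dropped out, and the Discussion (section 5) concedes that missing data may bias the results.

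**The concern.** Intention-to-treat needs outcomes from all randomised children, including those who stop the intervention. The withdrawal rules treat stopping or conflicting with the intervention as leaving the study, and no section separates the two. Children who might have been assessed at 3 months therefore become missing data because of the plan itself.

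This matters more if the missing scores differ from the observed ones. Section 2.11 says that a C-ACT of 19 or less indicates uncontrolled asthma and may call for stronger treatment, so the protocol itself links a poor primary outcome to a treatment change. A change of condition is also named as a trigger. The rules are worded by reference to the intervention, which only one arm receives. If the arm with more removals loses its worse-controlled children, its observed mean is too favourable.

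The feasibility aims are affected as well. The reported dropout rate would mix removals made by rule with true loss to follow-up, and the variability that section 2.4 wants to estimate could be understated.

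**Working it through.** **1. The plan's own figure.** The only number tied to withdrawals is the 20% attrition allowance in 2.4: 50 × 1.20 = 60 (30 per group), as stated. If 20% of 60 are lost, 60 × 0.80 = 48 remain (24 per arm), below the target of 50. How the allowance was computed is a separate small matter. Here it shows only that there is no slack to spend on children who could have been measured.

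**2. The rules against the analysis.**

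| Event | What the article prescribes | 3-month C-ACT provided for afterwards? |
|---|---|---|
| Serious event that interrupts the intervention (2.3.3) | removed from the study | not stated |
| Condition changes, or treatment altered in conflict with the intervention (2.3.3) | excluded | not stated |
| Family leaves the AI-HEALS arm (2.6) | attrition case; interview if feasible | not stated |
| All randomised children (2.12) | intention-to-treat, with multiple imputation | needed, measured or imputed |

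The last row is compatible with the first three only if the missing scores are imputed.

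**3. What imputation can use.** A removed child has a baseline C-ACT and, if removed later, a discharge C-ACT. The parent items look back four weeks (2.11), so neither score describes control after discharge. Standard chained-equations imputation assumes that missingness is explained by observed data. It corrects that part of the difference and no more. Predictive mean matching also draws its donors from children who stayed.

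**4. Complete-case illustration.** Let removed children score D points lower at 3 months than retained children, and let r be the share removed from an arm.

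- True arm mean: μ = (1 − r) × retained mean + r × (retained mean − D) = retained mean − rD.
- So the retained mean is μ + rD, and the bias in the arm difference is D × (r1 − r0), in favour of the arm that loses more.

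The documents give neither D nor the removal rates. Assumed values:

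| D (C-ACT points) | r1 − r0 = 0.10 (3 of 30) | r1 − r0 = 0.20 (6 of 30) |
|---|---|---|
| 2 | 2 × 0.10 = 0.2 | 2 × 0.20 = 0.4 |
| 5 | 5 × 0.10 = 0.5 | 5 × 0.20 = 1.0 |

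**5. The same in SD units.** If a share p of one arm is removed, and the propensity for removal correlates ρ with a normal outcome, the observed mean of that arm shifts by ρ × φ(z_p)/(1 − p), where φ is the standard normal density and z_p the normal quantile at p.

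| p | ρ = 0.3 | ρ = 0.5 | ρ = 1 |
|---|---|---|---|
| 5% | 0.03 | 0.05 | 0.11 |
| 10% | 0.06 | 0.10 | 0.20 |
| 20% | 0.11 | 0.18 | 0.35 |

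Again p and ρ are assumptions, and these shifts are before any imputation.

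**The case against.** The strongest reply is that nothing here contradicts intention-to-treat. No analysis set omits these children, imputation can keep them in their randomised arm, calling a family an attrition case is only a status label, and barring a switch to control is what intention-to-treat requires. Most of this stands. A reader might infer a flat contradiction, but the text does not go that far. What remains is that post-removal outcomes are not provided for, so the principle would be met by imputation where measurement may have been possible.

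The triggers are also qualified. A serious event counts only if it interrupts the intervention, and the examples are a heart attack and severe infection, not worsening asthma. A treatment change counts, on the natural reading, only if it conflicts with the intervention. Treatment adjustments belong to the standard care of both arms (2.7.1) and do not obviously conflict with question-answering, reminders and articles. A treatment change can also follow improvement. So it would be wrong to infer that every treatment change or serious event leads to removal. The link to the outcome is plausible, and strongest if a change of condition is a trigger on its own, as the sentence permits.

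A reader might also infer that removal must differ between arms. It need not: a change of condition can occur in either arm. The wording makes an imbalance possible, not certain.

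Finally, the trial is a pilot that section 2.4 says is not designed for hypothesis testing. Yet the Abstract and Discussion make improved asthma control the main purpose, and section 2.12 plans two-sided tests at 0.05. The pilot label lowers the stakes without removing them.

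**Conclusion.** The point holds as a defect in the follow-up rules. Sections 2.3.3 and 2.6 end participation for reasons plausibly related to asthma control, no section keeps these children in outcome collection, and section 2.12 then relies on imputation that corrects only what observed data explain.

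The size cannot be derived from the documents. The 0.2 to 1.0 point range is a complete-case illustration resting on assumed score differences of 2 and 5 points and an assumed 10 to 20 percentage-point imbalance in removal. It should not be read as an estimate of bias in the planned analysis. Once baseline and discharge scores enter the imputation, it is likely an upper guide for those inputs. With equal removal rates and equal D in the two arms, the formula gives zero.

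The planned comparison of dropouts and the general caution about missing data do not close the gap, because 3-month scores not collected cannot be recovered later.

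**What to change.** In sections 2.3.3 and 2.6, separate discontinuing the intervention from withdrawing from follow-up:

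- Whatever is decided clinically about the intervention or treatment, invite the child to the scheduled 3-month C-ACT and lung function assessment, and analyse in the randomised arm, unless consent for data collection is withdrawn.
- Count only withdrawn consent or true loss to follow-up as attrition. Report discontinuation of the intervention separately, by arm and reason.
- Keep multiple imputation for all remaining missing data, including missed visits, missing items and missing covariates.

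This takes no position on when treatment or the intervention should be changed or stopped.

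The cost is revised protocol and consent wording, with the approvals that section 3 requires, and some effort to stay in contact with families who stopped the intervention. The 3-month assessment is already in Table 1, so no new visit is needed. The change should be made as early in enrolment as possible.
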